## Abstract

**Background:**

Optimising the use of antibiotic agents is a pressing challenge to overcoming the rapid emergence and spread of multidrug-resistant pathogens in intensive care units (ICUs). Although Gram staining may possibly provide immediate information for predicting pathogenic bacteria, Gram stain-guided initial antibiotic treatment is not well established in the ICU setting. We planned the GRam stain-guided Antibiotics ChoicE for Ventilator-Associated Pneumonia (GRACE-VAP) trial to investigate whether Gram staining can safely restrict the use of broad-spectrum antibiotics in patients with ventilator-associated pneumonia (VAP), which is one of the most common hospital-acquired infections in ICUs.

**Methods/design:**

The GRACE-VAP trial is a multicentre, randomised, open-label parallel-group trial to assess the non-inferiority of Gram stain-guided initial antibiotic treatment to guidelines-based initial antibiotic treatment for the primary endpoint of clinical response rate in patients with VAP. Secondary endpoints include the coverage rates of initial antibiotic therapies, the selected rates of anti-pseudomonal agents and anti-methicillin-resistant *Staphylococcus aureus* (anti-MRSA) agents as initial antibiotic therapies, 28-day all-cause mortality, ICU-free days, ventilator-free days and adverse events. Patients are randomly assigned to receive Gram stain-guided treatment or guidelines-based treatment at a ratio of 1:1. In the Gram stain group, results of Gram staining of endotracheal aspirate are used to guide the selection of antibiotics. In the guidelines group, the combination of an anti-pseudomonal agent and an anti-MRSA agent is administered. A total sample size of 200 was estimated to provide a power of 80% with a one-sided alpha level of 2.5% and a non-inferiority margin of 20%, considering 10% non-evaluable patients.

**Discussion:**

The GRACE-VAP trial is expected to reveal whether Gram staining can reduce the use of broad-spectrum antibiotics without impairing patient outcomes and thereby provide evidence for an antibiotic selection strategy in patients with VAP.

**Trial registration:**

Clinicaltrials.gov, NCT03506113. Registered on 29 March 2018.

University Hospital Medical Information Network, UMIN000031933. Registered on 26 March 2018.

**Electronic supplementary material:**

The online version of this article (10.1186/s13063-018-2971-2) contains supplementary material, which is available to authorized users.

## Background

The increasing prevalence of infections caused by multidrug-resistant (MDR) organisms in intensive care units (ICUs) is recognised as a significant health threat all over the world [1, 2]. However, the development of new pharmaceutical agents is dwindling. Therefore, antibiotic options for the treatment of MDR organisms are becoming increasingly limited [3, 4]. To alleviate this issue, optimising the use of antibiotic agents has been emphasised [5].

Antibiotics are extensively used in ICUs because of the increased risks of infection due to underlying diseases or conditions, impaired immunity, and exposure to multiple invasive devices. In fact, the Extended Prevalence of Infection in Intensive Care II study showed that 51% of patients were considered to be infected during their stay in ICUs [6]. Ventilator-associated pneumonia (VAP) is an important complication that generates a need for antibiotic administration in patients with mechanical ventilation because it is one of the most common hospital-acquired infections in ICUs [6–8]. Therefore, the overuse of broad-spectrum antibiotic agents in patients with VAP could be a major cause of the accelerated emergence of antimicrobial-resistant organisms [9]. The 2016 clinical practice guidelines [10] for VAP published by the Infectious Diseases Society of America (IDSA) and the American Thoracic Society (ATS) recommend that an empirical treatment should include coverage for methicillin-resistant *Staphylococcus aureus* (MRSA) and *Pseudomonas aeruginosa*. Although empirical broad-spectrum treatments help to ensure that infections are treated effectively, overuse of broad-spectrum antibiotic agents leads to an increase in antimicrobial-resistant organisms. Thus, there is an increasing need to establish methods to safely reduce the use of broad-spectrum antibiotic agents for VAP.

In this trial, we will adopt a traditional but credible method, the Gram stain, to estimate pathogens of VAP. Gram staining of respiratory samples is potentially useful to guide appropriate initial antibiotic therapy. Several studies have evaluated the correlation between the results of Gram staining and culture, but the results were conflicting [11–16]. Furthermore, the evidence for Gram stain-guided initial antibiotic treatment for VAP is not well established. Therefore, whether the results of Gram staining are accurate enough to safely restrict the use of broad-spectrum antibiotics is still controversial.

We hypothesise that antibiotic treatment based on Gram stain results can restrict the administration of broad-spectrum antibiotic agents for VAP without detrimental effects on patient outcomes. Thus, we planned the GRam stain-guided Antibiotics ChoicE for VAP (GRACE-VAP) trial to investigate whether Gram stain-guided antibiotic treatment is non-inferior to guidelines-based treatment with respect to the clinical response rate in patients with VAP.

## Methods/design

### Design

We will conduct a multicentre, open-label, randomised, non-inferiority trial with blinded endpoint assessment that will compare the Gram stain-guided treatment with standard antibiotic treatment for patients with VAP. The final trial report will follow the Consolidated Standards of Reporting Trials (CONSORT) statement and its extension to non-inferiority and equivalence trials [17]. This study was registered at clinicaltrials.gov under the registry number NCT03506113. The study protocol was written in accordance with the Standard Protocol Items: Recommendations for Interventional Trials (SPIRIT) guidelines (Additional file 1).

### Patients

All patients admitted to the ICU will be screened every day during their ICU stay by the study investigators. The study participants will be enrolled in this study if they meet all of the inclusion criteria and none of the exclusion criteria. Patients will be included if they (1) are aged 15 years or older; (2) have undergone mechanical ventilation for at least 48 h; and (3) are diagnosed as having VAP, which is defined by a modified clinical pulmonary infection score of 5 or more [18].

Patients will be excluded if they (1) have an allergy to study medications, (2) are pregnant, (3) have already been discharged from the ICU, (4) are diagnosed as having heart failure or atelectasis, (5) have been administered antibiotics for more than 24 h when they meet the inclusion criteria, (6) are declined to provide full life support, or (7) are judged as inappropriate for inclusion at the discretion of the study physician.

### Ethics and informed consent

The clinical trial will be carried out according to the principles of the Declaration of Helsinki and Ethical Guidelines for Medical and Health Research Involving Human Subjects published by the Ministry of Health, Labour and Welfare of Japan and the Japanese Ministry of Education, Culture, Sports, Science and Technology. The study protocol was approved by the ethics committees of each participating hospital. Written informed consent will be obtained from all patients or their representatives.

### Randomisation and allocation concealment

Patients are randomly allocated to each treatment arm at a 1:1 ratio no earlier than 1 day before starting antibiotic therapy for VAP. Randomisation will be performed with the use of a stochastic minimisation procedure stratified by study centre, presence of chronic obstructive pulmonary disease, presence of traumatic brain injury, presence of post-cardiopulmonary arrest syndrome, and prior antibiotic therapy during the hospitalisation. We will use an electronic data capture system to conduct randomisation and data collection.

### Trial interventions

Treatment of patients in this trial follows a pragmatic approach. All study medications are commercially available and approved in Japan. They are used as marketed in standard dosage regimens. According to their treatment group, patients will receive either antibiotics selected according to the results of Gram staining or standard therapy based on the IDSA/ATS guidelines [10] (Fig. 1).

**Fig. 1 Fig1:**
[figure not shown]
Study design. *GPB* Gram-positive bacilli, *GPC* Gram-positive cocci, *GNR* Gram-negative rods, *ICU* Intensive care unit, *MRSA* Methicillin-resistant *Staphylococcus aureus*, *VAP* Ventilator-associated pneumonia

In the Gram stain group, the results of Gram staining of endotracheal aspirate are used to guide the selection of antibiotics. The results of the Gram stains are categorised as Gram-positive cocci (GPC) chains, GPC clusters, Gram-positive bacilli (GPB), Gram-negative rods (GNR), or a combination of these. A non-pseudomonal β-lactam antibiotic is selected when the Gram stain of the endotracheal aspirate shows only GPC chains and/or GPB. An anti-MRSA agent is selected when the Gram stain results show GPC clusters without GNR. An anti-pseudomonal agent is selected when the Gram stain results show GNR without GPC clusters. The combination of an anti-pseudomonal agent and an anti-MRSA agent is selected when the Gram stain results show both GPC clusters and GNR. We escalate an initial treatment selection process to cover pathogens isolated from respiratory samples before the onset of VAP if the Gram stain results suggest their involvement.

In the standard group, patients are administered the combination of an anti-pseudomonal agent and an anti-MRSA agent according to IDSA/ATS guidelines, because 47.7% of *S. aureus* isolates are MRSA in Japanese ICUs (https://janis.mhlw.go.jp/report/open_report/2016/3/1/ken_Open_Report_201600.pdf). If drug-resistant pathogens are isolated from respiratory samples before the onset of VAP, we escalate an initial treatment selection process to cover them. In both groups, specific antibiotic agents are selected according to previously recorded antimicrobial resistance patterns in each ICU.

The study medication can be de-escalated or escalated to a definitive treatment level according to the results of the pathogens isolated from respiratory samples. Dose adjustments in individual patients are performed as judged appropriate by the site investigator. Study medications are continued for at least 7 days and discontinued on the basis of the site investigator’s judgement.

### Assessment and follow-up

Clinical assessments are performed at baseline and daily throughout the study treatment, at the end of therapy (EOT) and at the follow-up/test of cure (FU/TOC) visit (Fig. 2). Laboratory assessments such as renal function, liver function, platelet count and inflammatory markers including white blood cell count, C-reactive protein and procalcitonin will be performed on the randomisation day; days 2, 4, 6, 8 and 14; and at EOT. Endotracheal aspirates and blood samples for bacterial culture will be obtained on the day of randomisation. We will collect data on all pathogens isolated with at least 1+ semi-quantitative growth from endotracheal aspirates, all pathogens isolated from blood, and antibiotic sensitivity. We will also collect data on all antibiotic agents administered during the VAP treatment, the presence of escalation or de-escalation and the length of the antibiotic therapies. Patients are followed for 28 days to evaluate efficacy and safety variables. If a patient is discharged from hospital prior to 28 days after randomisation, the investigators will contact the patient (or the patient’s representative as appropriate) by telephone to determine the patient’s disposition and status.

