### Outcome measures

The primary outcome is the clinical response rate at FU/TOC. Clinical response is defined as that fulfilling all four of the following components: completion of antibiotic therapy within 14 days, improvement or lack of progression of baseline radiographic findings at EOT, and resolution of signs and symptoms of pneumonia at FU/TOC. The signs and symptoms of pneumonia are defined as body temperature ≥ 38 °C, increase in purulent sputum and deterioration of oxygenation. The site investigators will collect information relevant to the clinical response described above. On the basis of these individual data, blinded evaluators on the event adjudication committee will judge the achievement of primary outcome.

The secondary outcomes are the coverage rate of initial antibiotic therapies, the selected rates of anti-pseudomonal agents and anti-MRSA agents as initial antibiotic therapies, 28-day mortality, 28-day ICU-free days, 28-day ventilator-free days, and adverse events. Therapy will be considered appropriate when all pathogens isolated with at least 1+ semi-quantitative growth from endotracheal aspirates are covered by the selected antibiotic agents. Safety outcomes are death during the study period and any adverse events reported at FU/TOC, including renal impairment, thrombocytopenia, diarrhoea, *Clostridium difficile* infection, skin rash and seizure.

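### Renal impairment and thrombocytopenia are counted as adverse events reported at FU/TOC, with no stated link to the serial laboratory values and no stated blinding

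*Protocol article*

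**What the plan says.** All references are to the protocol article.

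- **Assessment and follow-up, laboratory tests.** "Laboratory assessments such as renal function, liver function, platelet count and inflammatory markers" are scheduled; they "will be performed on the randomisation day; days 2, 4, 6, 8 and 14; and at EOT". FU/TOC is not among these time points.
- **Assessment and follow-up, clinical visits.** "Clinical assessments are performed at baseline and daily throughout the study treatment, at the end of therapy (EOT) and at the follow-up/test of cure (FU/TOC)". This is the only place in the section where FU/TOC is named.
- **Assessment and follow-up, duration.** "Patients are followed for 28 days to evaluate efficacy and safety variables".
- **Outcome measures, secondary outcomes.** The list ends with "28-day mortality, 28-day ICU-free days, 28-day ventilator-free days, and adverse events".
- **Outcome measures, safety.** Besides death, the safety outcomes are "any adverse events reported at FU/TOC, including renal impairment, thrombocytopenia, diarrhoea" and three further named events. No sentence says whether the two laboratory events come from the serial values.
- **Design.** The trial is described as an "open-label, randomised, non-inferiority trial with blinded endpoint assessment". Outcome measures gives the event adjudication committee's blinded evaluators one task, judging the primary outcome.

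The schedule figure (Fig. 2) is not visible, and the visible text gives no study day for FU/TOC.

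**The concern.** Renal impairment and thrombocytopenia are laboratory quantities, and the trial measures them at fixed days in both arms. Yet the outcome definition ties them to what is reported at one visit. A creatinine rise or platelet fall in the first week may have resolved by then. If events are instead gathered up to the visit, someone must still decide that a measured change is an adverse event. No blinding of that decision is stated.

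Treatment differs visibly between arms. Under Trial interventions, the standard arm starts an anti-pseudomonal plus an anti-MRSA agent, while the Gram stain arm may start with less. Someone who knows the arm could look harder for toxicity under the combination, or be slower to record it under the restricted regimen.

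The trial asks whether broad-spectrum use can be restricted safely, and adverse events are a named secondary outcome. A difference in these harms, or its absence, will be read as part of the answer. Values already in the database could largely settle it.

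**Working it through.** **1. The plan's own figure.** The only sample size concerns the primary outcome. With 67.8% response in both arms, a margin of 20 points, one-sided 2.5% and 80% power:

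n = (1.96 + 0.84)² × 2 × 0.678 × 0.322 / 0.20² ≈ 85.7, so 86 per group, as stated.

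It does not bear on this point. The document gives no rate for either harm.

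**2. The two sections side by side.**

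| Item | Assessment and follow-up | Outcome measures |
|---|---|---|
| Renal function, platelets | Randomisation day, days 2, 4, 6, 8, 14, EOT | Not mentioned as a source |
| FU/TOC | Clinical assessment | Point at which adverse events are reported |
| Who judges | Not stated for harms | Blinded committee, primary outcome only |

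The sections do not contradict each other: one says when tests are done, the other when events are reported. What is open is whether the first feeds the second.

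**3. Reading A: status at the visit.** Resolved events are lost. Assume (not in the documents) true rates of 30% v 15%, 100 per arm, a two-sided 5% test of two proportions, and the same captured share c in both arms. The observed difference is c × (30 − 15) points.

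| c | Observed rates | Difference | Power |
|---|---|---|---|
| 100% | 30% v 15% | 15 points | 72% |
| 75% | 22.5% v 11.25% | 11.25 points | 57% |
| 50% | 15% v 7.5% | 7.5 points | 39% |

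Even capture therefore creates no false difference, but it shrinks a real one.

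**4. Reading B: events accumulated up to the visit.** Let the true rate be p in both arms and let the share of cases reported differ between arms by g. The spurious difference is p × g. For example, with p = 20% and 90% v 70% reported, 0.20 × 0.90 = 18% v 0.20 × 0.70 = 14%, a gap of 4 points.

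| True rate p | g = 0 | g = 10 points | g = 20 points |
|---|---|---|---|
| 10% | 0 | 1 point | 2 points |
| 20% | 0 | 2 points | 4 points |
| 30% | 0 | 3 points | 6 points |

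Both p and g are assumptions. If g is zero, so is the artefact.

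**5. Scale.** At 18% v 14% with 100 per arm, the 95% half-width for the difference is 1.96 × √[(0.18 × 0.82 + 0.14 × 0.86)/100] ≈ 10 points. A 4-point artefact sits inside the sampling error. It would shift the estimate but would be unlikely to produce a significant result alone.

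**The case against.** A reader might infer that the plan takes site reports in place of the measured values, or that only a patient's state on the day of FU/TOC counts. The document supports neither. It does not say who reports the events, does not say the laboratory values are disregarded, and does not restrict the count to that day. The ordinary sense may well be cumulative. Tests on the randomisation day, five further days and EOT, daily clinical assessment during treatment and 28-day safety follow-up would let a transient change be seen and then reported. FU/TOC may also coincide with a listed laboratory day such as day 14, or Fig. 2 may list tests there.

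Three further points are fair. Thresholds and grading are commonly left to the full protocol or analysis plan, so their absence from an article is no fault. Limiting blinded adjudication to the primary outcome is a common choice, and analyses beyond the primary endpoint are called exploratory. The article claims no toxicity advantage; its Discussion lists bedside access, low cost and ease of learning. The exposure contrast is also less than complete, since Gram stain patients may receive either agent class or both.

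All of this stands, and it limits the point. It does not remove it. On the cumulative reading the serial values make an event visible, but counting it still depends on a report made without stated blinding. On the other reading, resolved events drop out wherever FU/TOC falls.

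**Conclusion.** The point holds in a limited form. The stated ascertainment of two laboratory harms is by report, in an open-label trial, with no stated link to the serial values and no stated blinding for these events. The exposure is to lost transient events or to differential reporting, depending on what the FU/TOC wording means.

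The size of any bias cannot be determined from the document. The 0 to 6 points rest wholly on an assumed true rate of 10% to 30%, equal in both arms, and an assumed reporting gap of 0 to 20 points. The power figures rest on assumed rates and capture. None of these numbers is evidence that reporting will differ between arms.

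This is a minor to moderate point on a secondary safety outcome. It leaves the primary analysis and the sample size untouched. It is worth making because the correction uses data already scheduled for collection.

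**What to change.** In Outcome measures:

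- State that renal impairment and thrombocytopenia are **also** derived centrally, without knowledge of arm, from all scheduled values after randomisation. Compare them with the randomisation-day value by one pre-specified published grade, in all randomised patients. The data centre described under Trial oversight could apply the rule.
- Keep reported adverse events through day 28 as a supplement. Scheduled values alone would miss events after the last scheduled test and events found only on unscheduled tests.
- Say whether reporting at FU/TOC is cumulative, and show derived and reported rates separately by arm.
- Leave diarrhoea, *C. difficile* infection, rash and seizure as reported events.

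The cost is small: no added tests, no change to treatment and no change to sample size. There are two drawbacks. Rates will rise in both arms because transient changes are counted. Values will also be missing after early death or discharge, since follow-up after discharge is by telephone for disposition and status; the number of patients with missing scheduled values should be given by arm.

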**Fig. 2 Fig2:**
[figure not shown]
Schedule of assessments. *ICU* intensive care unit, *SOFA* Sequential Organ Failure Assessment

### Outcome measures

The primary outcome is the clinical response rate at FU/TOC. Clinical response is defined as that fulfilling all four of the following components: completion of antibiotic therapy within 14 days, improvement or lack of progression of baseline radiographic findings at EOT, and resolution of signs and symptoms of pneumonia at FU/TOC. The signs and symptoms of pneumonia are defined as body temperature ≥ 38 °C, increase in purulent sputum and deterioration of oxygenation. The site investigators will collect information relevant to the clinical response described above. On the basis of these individual data, blinded evaluators on the event adjudication committee will judge the achievement of primary outcome.

The secondary outcomes are the coverage rate of initial antibiotic therapies, the selected rates of anti-pseudomonal agents and anti-MRSA agents as initial antibiotic therapies, 28-day mortality, 28-day ICU-free days, 28-day ventilator-free days, and adverse events. Therapy will be considered appropriate when all pathogens isolated with at least 1+ semi-quantitative growth from endotracheal aspirates are covered by the selected antibiotic agents. Safety outcomes are death during the study period and any adverse events reported at FU/TOC, including renal impairment, thrombocytopenia, diarrhoea, *Clostridium difficile* infection, skin rash and seizure.

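### The primary endpoint announces four components, prints three, and does not say how pneumonia re-treated between EOT and FU/TOC is scored, so a re-treated relapse can count as a response

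*Protocol article*

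**What the plan says.** The endpoint is set in the protocol article under Outcome measures. Its time point is clear: "The primary outcome is the clinical response rate at FU/TOC". The definition opens with "Clinical response is defined as that fulfilling all four of the following components", but only three follow: "completion of antibiotic therapy within 14 days, improvement or lack of progression of baseline radiographic findings at EOT, and resolution of signs and symptoms" (the last judged at FU/TOC). The signs are then specified: "The signs and symptoms of pneumonia are defined as body temperature ≥ 38 °C, increase in purulent sputum and deterioration of oxygenation". Site investigators supply the information relevant to this definition, and "blinded evaluators on the event adjudication committee will judge the achievement of primary outcome".

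Two other sections bear on the point. Assessment and follow-up describes the antibiotic record: "We will also collect data on all antibiotic agents administered during the VAP treatment", together with escalation or de-escalation and the length of therapy. Trial interventions (text after Fig. 1) sets when treatment ends: "Study medications are continued for at least 7 days and discontinued on the basis of" the site investigator's judgement.

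No section mentions relapse, recurrence or a restarted course after EOT, either as a component of response or as a secondary outcome.

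**The concern.** The three printed criteria look at three things: whether therapy was completed by day 14, the film at EOT, and the signs at FU/TOC. What happens between EOT and FU/TOC enters only through the patient's state at the final visit. A second antibiotic course can restore that state, so a patient for whom the first course failed may be recorded as a success.

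This matters more in a non-inferiority trial than in a superiority trial. Scoring failures as successes in the arm that has more of them shrinks the observed difference and favours the new strategy. Initial coverage can be narrower in the Gram stain arm by design, so an excess of relapse there is conceivable. Treatment also ends at the investigator's discretion in an open-label trial, so the length of the EOT-to-FU/TOC interval can differ between patients.

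The four-against-three mismatch is part of the same problem. Either a component is missing from the printed endpoint or the number is wrong. Correcting the number alone would leave the scoring of re-treatment open.

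**Working it through.** **1. The relapse case against the printed criteria.** Take, as an illustration, a patient who stops on day 8 with a stable film, relapses and restarts antibiotics on day 10, and has no listed sign at FU/TOC.

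| Criterion | 14-day criterion means the first course | 14-day criterion means all pneumonia therapy |
|---|---|---|
| Therapy completed within 14 days | Met (day 8) | Met only if the second course ends by day 14, four days after restart |
| Film at EOT | Met, since the film precedes the relapse | Unclear which EOT applies |
| Signs resolved at FU/TOC | Met, after the second course | Met, after the second course |
| Result | Responder, 3 of 3 | Depends on the second course |

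In the second column, if the stated minimum of 7 days also applied to the restarted course, this patient would run past day 14 and fail. If it did not apply, a short second course would leave the patient a responder. The text settles neither question. A patient who still has signs at FU/TOC fails under both readings.

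**2. The plan's own sample size.** Inputs from Sample size: response 67.8% in both arms, margin 20 points, power 80%, one-sided level 2.5%.

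n = (1.960 + 0.842)² × 2 × 0.678 × 0.322 / 0.20² = 7.849 × 0.4366 / 0.04 = 85.7, so 86 per group. The stated figure reproduces (power 80.1%).

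**3. How large an observed deficit still passes.**

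SE = √(2 × 0.678 × 0.322 / 86) = 0.0713

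Largest passing deficit = 0.20 − 1.96 × 0.0713 = 0.060, about 6 points.

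**4. Effect on the error rate.** The article gives no rate of re-treated relapse, so the shares below are assumptions. Let response with re-treatment counted as failure be 67.8% (standard) and 47.8% (Gram stain), exactly at the margin, with 86 per group. Add to each arm the share of patients re-treated and well at FU/TOC. Then P(declare non-inferiority) = Φ((0.20 − d)/SE − 1.96), where d is the apparent difference and SE is the unpooled standard error at the apparent rates.

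| Re-treated and counted as responders, standard vs Gram stain | Apparent difference | P(declare non-inferiority) |
|---|---|---|
| Equal shares, 2% to 10% | 20 points | 2.5% |
| 2% vs 5% | 17 points | 6.1% |
| 2% vs 7% | 15 points | 10.1% |
| 5% vs 10% | 15 points | 10.3% |
| 5% vs 15% | 10 points | 29.2% |

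Example, 5% vs 10%: rates 72.8% and 57.8%; SE = √((0.728 × 0.272 + 0.578 × 0.422)/86) = 0.0717; (0.20 − 0.15)/0.0717 − 1.96 = −1.26; Φ = 10.3%.

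The apparent difference falls by exactly the between-arm excess. The overall level of re-treated relapse hardly matters.

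**The case against.** **The printed list is visibly incomplete.** It promises four components, so the omitted one might deal with re-treatment and close the gap. This stands as a limit: the article does not say what the fourth is, and linking it to re-treatment would be a guess. It also means that the printed definition cannot be applied with certainty to this patient.

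**The 14-day criterion may already catch these patients.** It does not say first course, and on the wider reading many re-treated patients would fail. That is a fair reading, but it is not stated, and it makes failure depend on when the second course ends rather than on the relapse.

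**The data may be captured anyway.** Re-treatment of a relapse could be regarded as VAP treatment, patients are followed for 28 days, and the schedule in Fig. 2 is not shown. Form-level detail belongs in the full protocol. So it cannot be said that a restart would be missed, only that the printed wording does not clearly include it. Capture would not in itself settle the scoring.

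**Direction is assumed.** Treatment in both arms can be changed once culture results arrive, which weakens the link between initial choice and relapse after EOT. A reader might infer that the definition necessarily biases the trial towards non-inferiority. The documents do not support that: they give no relapse rates by arm, and equal shares leave both the difference and the error rate unchanged.

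**Conclusion.** The point holds in conditional form. As printed, the endpoint leaves unsettled how a relapse re-treated between EOT and FU/TOC is scored, and on a natural reading such a patient is a responder. It would go too far to say that every such patient counts as a success: that depends on the missing component, on the reading of the 14-day criterion, and on the patient being free of signs at FU/TOC.

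The size depends on an assumed excess of such cases in the Gram stain arm. An excess of 3 to 10 points, with true response exactly at the margin, raises the chance of wrongly declaring non-inferiority from 2.5% to between about 6% and 29%. With no excess the rate stays at 2.5%. Since the passing limit is only about 6 points of observed deficit, a few points could decide the trial. The timing of FU/TOC, and so the room for relapse and successful re-treatment, is not given in the text. The change should be made because it is cheap and it removes an ambiguity in the primary endpoint.

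**What to change.** 1. **Outcome measures:** state the fourth component, or correct the count to three.
2. **Outcome measures, in either case:** add that antibiotics restarted for pneumonia between EOT and FU/TOC, as judged by the blinded committee, count as non-response. State that the 14-day criterion refers to the initial course.
3. **Assessment and follow-up:** extend the antibiotic record through FU/TOC, with the indication for each course, and pass it to the adjudicators.
4. **Sample size:** confirm that the 67.8% was measured with the same definition.

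These are changes to endpoint scoring and data collection only and do not alter how patients are treated.

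**Cost:** protocol wording, a few more data entries, and a slightly lower response rate in both arms. If the 67.8% did not count re-treatment as failure, the planned number needs a check. For example, an assumed 5-point fall to 62.8% in both arms gives n = 7.849 × 2 × 0.628 × 0.372 / 0.04 = 91.7, so 92 per group, against 90 evaluable from 100 enrolled at 10% loss. Power with 90 is Φ(0.20/√(2 × 0.628 × 0.372/90) − 1.96) = Φ(0.82), about 79%, so the loss is small.
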